##### Intervention

The intervention will consist of a series of counseling and participatory workshops, planned based on the unique practice identified in Phase I. On the day of enrollment, women in the intervention arm will receive dual-method counseling with a tool developed based on the practice identified in Phase I, in addition to regular family planning counseling with an existing counseling tool [36]. The dual-method counseling will be conducted for 20–40 min by trained research assistants.

Two weeks after enrollment, women in the intervention arm will be invited for a 1-day participatory learning workshop (5 h) at the same health facilities where they were recruited. Women may decide whether to participate. The workshop will be facilitated by research assistants and positive deviants, using a training protocol developed after Phase I. It will include simulations and role-plays for successful communication about using a condom with their partners and a group discussion regarding family planning and HIV/STI risk.

Bi-monthly telephone counseling will be provided by positive deviants three times (3, 5, and 7 months after enrollment). Each counseling session will take 10–20 min and aim to remind women of the risk of unintended pregnancies and HIV/STIs and strengthen their capacity to communicate using a condom with their partners. The 2-month intervals can allow women to reflect on counseling messages, discuss the use of condoms with their partners, and put it into practice. Positive deviants, therefore, can provide more effective counseling tailored to participants’ individual needs through understanding their situation.

Women in the control group will be provided regular family planning counseling including dual-method use for 10–30 min by trained research assistants using the same existing tool on the day of enrollment [36]. Moreover, refresher training will be provided bi-monthly on family planning and HIV/STI risk via phone, by research assistants three times (3, 5, and 7 months after the enrollment).

Condoms will be provided for free, regardless of the allocation at the selected health facilities. Before the intervention starts, the research assistants will receive a 2-day training session about the contents of the existing counseling tool by health professionals [36].

##### Outcomes

The primary outcome is dual-method use. In this study, dual-method use is defined as the use of male or female condoms along with HECs such as pills, injectables, implants, male and female sterilization, and IUD consistently in the last 2 months, before each follow-up interview [8]. The outcome measure combines two questions regarding the frequency of condom use and HEC use. The frequency of condom use will be asked with an item: “How often did you and your partner use a male or female condom during the past 2 months?” Women will answer this question using a four-point scale “every time,” “almost every time,” “sometimes,” and “never.” Only those who answered “every time” will be considered as having consistent condom use. Women will also be asked if they have been using any HECs with a question, “Apart from condoms, have you been using any other forms of protection against pregnancy during the past two months?” Responses to these two questions will be used to construct the dual-method use outcome with the following categories: (1) dual-method use (consistent condom and HEC use); (2) inconsistent use of condoms and HECs; and (3) single or no use of contraceptive methods.

The secondary outcome is the self-reported first occurrence of pregnancy and STIs in the previous 2 months [37]. They will be assessed with the following two questions: “Have you been told by a healthcare provider that you got pregnant for the first time in the past 2 months?” and “Have you been told by a healthcare provider that you had any STIs such as chlamydia, gonorrhea, or trichomonas infection for the first time in the past 2 months?”

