#### Phase I: identify positive deviants

##### Sample size, eligibility, and recruitment

In Phase I, 150 women will be interviewed. This is based on the assumption that at least 7% of women would practice dual-method use [13] and at least 10 women who are considered as a positive deviant would be identified.

To be eligible for joining this study, participants should have the following characteristics: (1) women; (2) aged 18–49 years; (3) sexually active; (4) using HECs at the time of recruitment; (5) have a desire to avoid pregnancy for 12 months from recruitment; (6) have a husband or live-in sexual partner; and (7) have access to a valid phone number.

Being sexually active is defined as having had sexual intercourse in the 3 months before the study [13]. Pregnant women and women who are infertile for other reasons will be excluded from this study. Health workers, including community health workers, political and religious leaders, and teachers will also be excluded because they may not represent communities or be influenced by their occupations and social status.

For sampling, five health facilities will be selected purposively. Then, five trained female research assistants will approach female clients in the family planning sections of the selected health facilities. The first client will be selected randomly at each clinic and then every third client will be informed about the opportunity to participate in this study. If they are interested in participating, the research assistants will ask screening questions using a pretested questionnaire to check their eligibility for the study. This process will be repeated until the required sample size is met.

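### The follow-up item that stands in for HEC use accepts any non-condom method, so condoms plus a non-HEC method can be coded as dual-method use in the primary outcome

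*Protocol article*

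**What the plan says.** All references are to the protocol article. Under Phase II, Outcomes, it states: "The primary outcome is dual-method use". The definition, whose window is the 2 months leading up to a follow-up call, reads in part: "the use of male or female condoms along with HECs such as pills, injectables, implants, male and female sterilization, and IUD consistently in the last". The second method therefore has to be an HEC.

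On measurement, the same section says: "The outcome measure combines two questions regarding the frequency of condom use and HEC use". The condom item has a four-point frequency scale, and only the top answer counts as consistent. The second item is introduced with the words "Women will also be asked if they have been using any HECs with a question", but the question then printed is "Apart from condoms, have you been using any other forms of protection against pregnancy during the past two months". The construction rule follows: "Responses to these two questions will be used to construct the dual-method use outcome", with consistent condom and HEC use as the first of three categories.

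Two other sections matter. The eligibility criteria in Phase I, carried over to Phase II, require every woman to be using an HEC at recruitment. Other information lists the contraceptive methods in use among the items collected at the baseline interview. No follow-up item on the type of method is described.

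**The concern.** The definition names a class of methods and the item does not. The introduction to the item says that it asks about HECs, but a respondent hears only the printed question, and that question covers every form of protection other than condoms. Because the outcome is built from the two answers alone, the printed rule contains nothing that would remove a yes given for a non-HEC method.

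The trial enrols only HEC users who are not yet dual-method users. A woman can therefore miss the outcome in two ways: by not taking up consistent condom use, or by leaving her HEC. The condom item handles the first. The second is seen only through the broad item, which misses some women who leave HECs. What is at stake is whether the primary comparison estimates the quantity that the protocol defines, and how far the odds ratio is distorted if it does not.

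**Working it through.** **Step 1. Definition against item.** No figure in the protocol is at issue, so the main check is textual. Take four women who all report condom use every time and apply the printed rule:

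| Other method in the last 2 months | Truthful answer to second item | Coded | Under the definition |
|---|---|---|---|
| Still on a listed HEC | Yes | Dual-method | Dual-method |
| Left HEC, condoms only | No | Not dual-method | Not dual-method |
| Left HEC, now another non-condom, non-HEC method | Yes | **Dual-method** | **Not dual-method** |
| HEC for part of the window | Depends on how she reads the item | Unclear | Not consistent use |

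Only the third row is a clear error. It needs three things together: leaving the HEC, taking up a different non-condom method, and using condoms every time. The fourth row is an ambiguity: the item can be read as asking about ongoing use or about any use in the window.

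**Step 2. Do such methods exist in this population?** Study setting gives 35% contraceptive use among married women in Uganda in 2014 and 32% HEC use. The listed HECs add up: 19 + 6 + 3 + 2 + 2 = 32. That leaves 35 − 32 = 3 percentage points outside HECs, part of which may be condoms alone. The article names no specific non-HEC method.

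**Step 3. Illustration of size, equal miscoding in both arms.**

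- From the protocol (Phase II sample size): OR 2.43, ICC 0.006, 480 women per arm, 26% dropout, 20 facilities, 5% significance level (two-sided assumed).
- Assumed: control rate p. It is not stated for Phase II, so 5% and 7% are both shown. Of the two, 5% comes close to the stated minimum of 588 (it gives 584 without continuity correction); 7% is the prevalence assumed for Phase I.
- Assumed: a share s of women in each arm has moved to a non-HEC, non-condom method, and a fraction c of those uses condoms every time. Neither is in the protocol.

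Intervention rate: q = 2.43p / (1 − p + 2.43p), which gives 0.1134 for p = 0.05 and 0.1546 for p = 0.07.

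Retained per arm: 480 × 0.74 = 355.2. Mean cluster size recruited: 960 / 20 = 48. Design effect: 1 + (0.74 × 48 − 1) × 0.006 = 1.207. Effective number per arm: 355.2 / 1.207 = 294.

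Rates under the definition: (1 − s)p and (1 − s)q. Rates as measured: add s × c to each.

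Worked case, p = 0.07, s = 5%, c = 20%: the defined rates are 0.0665 and 0.1469. Adding 0.05 × 0.20 = 0.01 gives 0.0765 and 0.1569. The OR goes from (0.1469/0.8531) / (0.0665/0.9335) = 2.42 to (0.1569/0.8431) / (0.0765/0.9235) = 2.25.

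| p | s | c | OR defined | OR measured | Power defined | Power measured |
|---|---|---|---|---|---|---|
| 7% | 2% | 20% | 2.42 | 2.35 | 0.90 | 0.89 |
| 7% | 5% | 20% | 2.42 | 2.25 | 0.89 | 0.86 |
| 7% | 10% | 50% | 2.40 | 1.83 | 0.87 | 0.73 |
| 5% | 2% | 20% | 2.43 | 2.33 | 0.79 | 0.78 |
| 5% | 5% | 20% | 2.42 | 2.19 | 0.78 | 0.74 |
| 5% | 10% | 50% | 2.41 | 1.71 | 0.76 | 0.56 |

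Power is for a two-proportion comparison at the effective number per arm. The effect is small when few women switch and substantial only in the extreme case.

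**The case against.** The strongest reply is that a journal article condenses the instrument. The response format of the second item is not given, the questionnaire is not shown, and the text introducing the item says that it concerns HECs. The interviewers may well record the method. This stands as a limit on certainty. It does not remove the point, because the article prints both the question and the coding rule, and neither contains that step.

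It can also be said that few women are exposed to the error. All use an HEC at entry, all want to avoid pregnancy for 12 months, and follow-up lasts 8 months. That also stands, and it is why the size is called modest.

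Three stronger readings are tempting but not supported:

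- A reader might infer that the item would credit the intervention with success whenever it raised condom use while women left HECs. It would not: a woman who left for condoms alone can truthfully answer no and is coded correctly.
- A reader might infer that miscoding falls chiefly on the intervention side and could create an effect where there is none. Any figure for this needs an assumed control rate and miscoding confined to one arm. The Background describes HEC users being less likely to use condoms, not condom promotion driving women off HECs. Both arms receive counselling that covers dual-method use, and both have free condoms.
- A reader might object that the condom scale has no answer for a woman without intercourse in the window, since eligibility says only "Being sexually active is defined as having had sexual intercourse in the 3 months before the study". The definition requires condom use, so counting her as a non-user agrees with it. Setting such women apart in the main analysis would condition on behaviour after randomisation that the intervention may change.

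**Conclusion.** The point holds in a limited form. As printed, the second item is broader than the construct it is meant to measure, and the construction rule does not correct this. Women who combine consistent condom use with a non-HEC, non-condom method can enter the primary outcome against its definition.

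The amount cannot be derived from the protocol, which gives no rate of leaving HECs and no control rate for Phase II. If miscoding is equal in the two arms, the bias is toward the null: slight with 2% to 5% of women switched and one in five of those always using condoms, and marked only with 10% switched and half always using condoms. If it is unequal, the direction is open. The conclusion assumes that the questionnaire follows the article; if it already records the method at each call and codes on it, only the article's description needs correcting.

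This is worth settling before enrolment because the remedy is nearly free and a method that was never asked about cannot be reliably recovered at analysis.

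**What to change.** At each of the four follow-up calls (2, 4, 6 and 8 months), record which method was used, from the same list as at baseline, and whether it was used throughout the past 2 months. Code HEC use as yes only for the HECs named in the definition. The coverage question settles the part-window ambiguity and matches the definition's requirement of consistent use. State the coding rule in Outcomes. Keep women with no intercourse in the window as non-users in the main analysis.

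Cost: one or two extra response fields per call. The sample size and the model need no change.

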A trade-off between HEC and use of condoms is a barrier to practicing dual protection. Women are less likely to use condoms with their male partners when using HECs [16]. Use of condoms may become unacceptable, especially in marital sex, as it is perceived as protection against HIV/STIs rather than pregnancies. Both women and men may think condoms are unnecessary with an intimate partner, especially when women are using HECs. However, use of condoms is necessary for women who are at risk of HIV/STIs, regardless of use of HEC [17, 18]. Extramarital sexual relationships are common, especially among men, in SSA [19]. For instance, an estimated 44% of HIV infections occurred among married or cohabiting couples in Kenya [20].

Several interventions have been conducted to promote dual-method use in the USA [11, 12]. However, few interventions had a significant effect on dual-method use [11, 12, 21] and the impact of such interventions was often not sustainable [22]. In resource-limited settings, including SSA, no interventions have been examined, although people are at considerable risk of unintended pregnancies and HIV/ STIs [11]. Women and men may perceive the importance of the use of condoms for preventing HIV/STIs, but often do not practice it [23]. Motivating factors for dual-method use remain unknown when the percentage of such users is low.

The positive deviance approach has the potential to address barriers to sensitive issues such as sexual and reproductive health. This approach seeks behaviors that contribute to otherwise high-risk individuals, or positive deviants, remaining free from a disease or condition and enables communities to adopt such practices [24, 25]. This approach has addressed complex development challenges, which are often hard for expert outsiders to measure, such as gender-related and socio-cultural barriers [24]. For example, the positive deviance approach was applied to advocate against female genital mutilation using actual words of positive deviants in Egypt [24]. Use of condoms is not prevalent in SSA, especially among married women using HECs. Barriers to condom use are complex and it is often difficult for outsiders to grasp the whole picture [26]. Given the limited effect of previous interventions [11], the positive deviance approach could be an ideal option for promoting dual-method use.

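### The highly effective contraceptive (HEC) half of the primary outcome is scored from a question about any non-condom protection, so the stated rule can count non-HEC users as dual-method users and does not prompt for sterilization

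*Protocol article*

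**What the plan says.** The Outcomes section of the protocol article (Phase II) does four things in sequence.

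- It defines dual-method use as consistent use, over the last 2 months, of "male or female condoms along with HECs such as pills, injectables, implants, male and female sterilization, and IUD".
- It describes the measure: "The outcome measure combines two questions regarding the frequency of condom use and HEC use".
- It states what the second item is for: "Women will also be asked if they have been using any HECs with a question". The item then printed asks, apart from condoms, "have you been using any other forms of protection against pregnancy during the past two months". It names no method and does not restrict the answer to HECs.
- It states the scoring rule: "Responses to these two questions will be used to construct the dual-method use outcome with the following categories". The categories are dual-method use, inconsistent use of condoms and HECs, and single or no method.

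The Background describes HECs as hormonal methods, the non-hormonal IUD and sterilization. The type of contraceptive in use appears under Other information, among the items of the baseline interview. The article does not say that method type is recorded at the 2-, 4-, 6- and 8-month calls.

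**The concern.** The definition is specific to HECs; the item that operationalizes it is not. The trial is meant to show that women add consistent condom use while keeping a HEC. As described, the measure cannot tell a woman who kept her HEC from one who replaced it with another method. If method type is not captured at follow-up, no later analysis can recover the difference.

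The error can run both ways. Women on a non-HEC method plus condoms every time are counted as successes although the definition excludes them. A sterilized woman who always uses condoms meets the definition, but if she says she has not been using anything else she falls into the third category. At stake is whether the primary outcome measures what it is defined to measure, with some loss of power and possible bias if the errors differ between arms.

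**Working it through.** **Definition against scoring rule.**

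| Woman at follow-up, condoms every time | By the definition | By the printed item and rule |
|---|---|---|
| Still on pills, injectable, implant or IUD | Dual-method user | Dual-method user |
| Stopped HEC, uses a non-HEC method | Not a dual-method user | Dual-method user, since a truthful answer is yes |
| She or her partner is sterilized, answers yes | Dual-method user | Dual-method user |
| She or her partner is sterilized, answers no | Dual-method user | Single method |

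The second row follows directly from the text. The fourth depends on how a respondent understands the item and is an inference.

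**Inputs for a materiality check.** No stated figure in the plan is in dispute.

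- Study setting (married women, Uganda, 2014): any contraceptive 35%, HECs 32%, female sterilization 3%.
- Sample, eligibility, and recruitment (Phase II): odds ratio 2.43, two-sided 5%, 80% power, ICC 0.006, dropout 26%, 960 women, 20 facilities.
- The control-arm rate is not stated. I assume 5% to 8.5%. The lower end is close to what the minimum of 588 implies: at 5%, the two-proportion formula without continuity correction gives 584.

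**Shares.** Female sterilization is 3/32 = 9.4% of HEC use. Non-HEC use, condoms included, is at most 35 − 32 = 3 points, or 3/35 = 8.6% of contraceptive users. Applying these national shares to this cohort is an assumption.

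**Effective sample size.** 960 × 0.74 = 710 women analysed, or 355.2 per arm. Mean cluster size is 48 × 0.74 = 35.5, so the design effect is 1 + (35.52 − 1) × 0.006 = 1.207. Effective size per arm is 355.2/1.207 = 294.

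**Starting point at 5%.** The intervention rate is 2.43 × 0.05/(0.95 + 2.43 × 0.05) = 11.34%, and power is 80.3%.

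**Missed sterilized women, equal in both arms.** If all 9.4% answer no, both rates are multiplied by 0.906, giving 4.53% and 10.28%. The odds ratio is (0.1028/0.8972)/(0.0453/0.9547) = 2.41 and power is 76.0%. If half answer no, power is 78.2%.

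**False dual-method users, equal in both arms.** If 8.6% of women scored as dual-method users are really on a non-HEC method, both rates are divided by 1 − 0.086. At 5% they become 5.47% and 12.40%, with an odds ratio of 2.45.

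| Assumed control rate | Power, no error | Power, all sterilized women answer no | Odds ratio, same case | Odds ratio, 8.6% false dual-method users |
|---|---|---|---|---|
| 5% | 80.3% | 76.0% | 2.41 | 2.45 |
| 7% | 90.4% | 87.0% | 2.41 | 2.46 |
| 8.5% | 94.3% | 91.7% | 2.40 | 2.46 |

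**The case against.** The article states the item's purpose as HEC use, and trained interviewers put it from an interview guide that is not shown. That guide may hold a method probe. The article gives no response scale for this item, so it would be wrong to say that it is strictly yes/no or that method type is never asked. This stands. What remains is that the article prints the item and says the outcome is constructed from the two responses; that is a stated rule, not a detail left out.

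The sterilization argument leans on one English verb, while interviews may be in Runyankore, and every participant has already been identified as a HEC user at recruitment. This also stands: the no answer is a possibility, not a prediction.

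A false positive requires stopping the HEC, adopting a non-HEC method and using condoms every time, all in the same woman. This limits the likely size.

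A reader might go further and infer that the intervention would push women from HECs to condoms plus a weaker method, and that this would be scored as success. The Background does say that "A trade-off between HEC and use of condoms is a barrier to practicing dual protection", but it describes HEC use discouraging condoms, not condom uptake displacing HECs. One can construct a spurious effect. Suppose 3% to 8% of women are off HECs on another method, with consistent condom use of 10% to 20% among them in the control arm and 20% to 40% in the intervention arm. With true dual use of 4.96% in both arms, the apparent odds ratio is 1.06 to 1.30. For the top value, the observed rates are 4.96% + 8% × 10% = 5.76% and 4.96% + 8% × 30% = 7.36%. That arithmetic is right, but the scenario has the intervention doubling or tripling condom use only among women who stopped their HEC and doing nothing for the rest. It also gives both arms the same share of HEC stoppers, so it does not represent the displacement mechanism. The documents support neither the scenario nor its inputs.

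**Conclusion.** The point holds as a mismatch between the primary outcome's definition and its stated scoring. Followed literally, the rule counts some women outside the definition as dual-method users, and the item gives sterilized women, or women with sterilized partners, no prompt to report a method that the definition includes.

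The size of the error cannot be derived from the documents. Because all women enter on a HEC, it is probably modest. With errors equal between arms, the odds ratio stays between 2.40 and 2.46 against the planned 2.43. Power falls at worst from about 80% to 76%, which assumes a 5% control rate, the national 9.4% sterilization share, and every sterilized woman answering no. Differential error is possible, since the arms receive different counseling, but no figure in the documents bounds it. The point should be corrected because it concerns the primary outcome and is almost free to repair, not because a large bias has been shown.

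**What to change.** At each follow-up call, ask which methods other than condoms the woman or her partner used in the past 2 months, coded with the same list as the baseline item on contraceptive methods in use. Score the HEC component as yes only for pills, injectables, implants, IUD, and male or female sterilization; treat any other method as non-HEC. Carry sterilization of either partner recorded at baseline forward as HEC use. State this coding rule next to the outcome definition. If the interview guide already contains such a probe, it is enough to say so and to base the scoring on it.

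The cost is one reworded phone question and one coding rule, with a few seconds more per call. It is best done before enrollment starts.

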##### Data collection

On the day of enrollment, all women will be interviewed using a pretested structured questionnaire to identify basic baseline characteristics. They will then be followed up via phone bi-monthly for 8 months to assess how the intervention influences dual-method use and pregnancy and STI incidence (2, 4, 6, and 8 months after enrollment). All interviews will be conducted by trained female research assistants using an interview guide in either English or Runyankore. All data will be entered using EpiData version 4.6.

All participants will be given some incentives worth 10,000 UGX (equivalent to US$3) for their time and participation in the study after the initial interviews. Participants who participate in the learning workshop will receive 20,000 UGX (equivalent to US$6) for transportation.

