##### Data analysis

The background characteristics of women will be compared between the intervention and the control group using Pearson’s chi-squared or Fisher’s exact tests [44]. Mixed effects logistic regression analysis will be performed with a random effects term for the clusters to access the effect of the intervention on the following outcomes: dual-method selection and adherence; self-reporting pregnancy; and incidence of STI in the 2 months before each follow-up data collection. In addition, hierarchical logistic regression model will be introduced to ascertain the predictors of each outcome. Model 1 will be adjusted for demographic variables, such as age, education, and the number of children. Model 2 will be adjusted for the status of residence (urban or rural) in addition to demographic variables. Model 3 will include the type of HECs at the baseline sequentially, which is known to be associated with dual-method use [8, 45]. Model 4 will be adjusted for variables related to their partners, such as partner’s attitude toward family planning. Model 5 will include women’s perceived risk of HIV/STIs. Model 6 (full model) will be adjusted for all variables. Besides, sub-group analyses will be conducted among HIV-seroconcordant and -discordant couples. All the analyses will be conducted on both per-protocol and intention-to-treat bases. The per-protocol analysis will assess the efficacy of the intervention while the intention-to-treat analysis will test its effectiveness [46]. Rates of attrition and reasons for dropout will be compared between the intervention and the control groups [47]. The significance level will be set at 5%. STATA version 13.1 will be used for all data analyses.

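### Both secondary-outcome questions ask about an event for the first time, so a woman with an earlier pregnancy or STI can truthfully answer no to a new one, and incidence may be underestimated

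*Protocol article*

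**What the plan says.** The Outcomes section of Phase II defines the measure: "The secondary outcome is the self-reported first occurrence of pregnancy and STIs in the previous 2 months". Two items, printed word for word, assess it. The pregnancy item asks "Have you been told by a healthcare provider that you got pregnant for the first time in the past 2 months". The STI item asks whether a provider has told the woman that she "had any STIs such as chlamydia, gonorrhea, or trichomonas infection for the first time in the past 2 months".

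The Phase II data collection section gives the purpose of the phone calls as assessing dual-method use and "pregnancy and STI incidence (2, 4, 6, and 8 months after enrollment"). The data analysis section models, with mixed effects logistic regression, "self-reporting pregnancy; and incidence of STI in the 2 months before each follow-up data collection".

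Eligibility for Phase II follows Phase I apart from excluding current dual-method users: women aged 18–49 living with a husband or partner, sexually active and using a highly effective contraceptive. An earlier pregnancy or STI is not an exclusion. Reproductive history and STI history are recorded at baseline, and the first adjusted model includes "demographic variables, such as age, education, and the number of children".

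**The concern.** The items and the target differ. Incidence in a window counts any new pregnancy or STI diagnosis in it. The items add the phrase about a first time without saying what it is counted from. At least three readings are open: first in the woman's life, first since enrollment, or newly arisen in this window. Only the last matches the analysis section directly.

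A woman who has children and becomes pregnant during follow-up can, on the first reading, truthfully answer no. So can a woman treated for an STI before the trial who is diagnosed again. Her answer is stored exactly as that of a woman with no event. Baseline history shows who could have been misled, not who was, so the loss cannot be undone at analysis. At stake are the absolute incidence of both secondary outcomes and the number of events available to compare the arms.

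**Working it through.** The protocol states no event rate, sample size or power for these outcomes, so there is no figure to reproduce. The check sets the text side by side and then illustrates the possible loss.

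**1. Item against target**

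| Place | What is counted |
|---|---|
| Outcomes, definition | first occurrence, previous 2 months |
| Outcomes, both items | provider-told event, for the first time, past 2 months |
| Phase II data collection | incidence at 2, 4, 6 and 8 months |
| Data analysis | incidence in the 2 months before each call |

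The population includes women with earlier events: nothing excludes them, and number of children and STI history are planned variables.

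**2. Share of true events captured by the wording**

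Let s be the share of new events that occur in women with an earlier event of that kind, and r the share of those women who take the phrase as first ever. Neither is in the protocol; both are assumptions.

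Capture = 1 − s × r

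| | r = 0.25 | r = 0.50 | r = 1.00 |
|---|---|---|---|
| s = 0.2 | 95% | 90% | 80% |
| s = 0.5 | 87.5% | 75% | 50% |
| s = 0.9 | 77.5% | 55% | 10% |

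For example, 1 − 0.9 × 0.5 = 0.55. The column r = 1 is a bound, not an expectation. A high s may suit pregnancy and a lower s STIs, but the protocol fixes neither.

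**3. What this does to the comparison**

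If capture c is the same in both arms and there are no false positives, the observed risk ratio is (c × p1)/(c × p0) = p1/p0. It is unchanged, and the odds ratio nearly so when events are rare. The risk difference becomes c × (p1 − p0). With rare events, and setting clustering aside, the variance of the log risk ratio is about 1/e1 + 1/e0, where e1 and e0 are the event counts. Multiplying both counts by c inflates the standard error by 1/√c: 1.03 at c = 0.95, 1.15 at c = 0.75, 1.35 at c = 0.55.

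**4. Missed calls, as a separate matter**

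Four calls × 2 months = 8 months, so the windows meet without overlap. If the month-4 call is missed and month 6 completed, neither printed question covers an event in months 2–4: 2/8 = 25% of that woman's follow-up. That window is a missing outcome. It leaves the denominator as well as the numerator, so it is not a false no.

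**The case against.** The best defense is context. The sentence just before the items speaks of occurrence within 2 months, and later sections speak of incidence. With calls every 2 months, the phrase has an evident purpose: not recording one continuing pregnancy at several calls. Trained interviewers work from a guide, and the same contact person stays with each woman. The Runyankore wording, the guide and the source cited for the outcome are not shown, so how the item sounds to a respondent is partly unknown. This stands as a reason not to claim that an undercount will occur or how large it is. It does not justify keeping the phrase. If the intended meaning is a new event in this window, deleting the words loses nothing, and double counting can be prevented by recording a date.

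A second objection is that both arms hear the same item. This also stands: the expected harm is lost events and low incidence, not a distorted ratio.

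A reader might go further and infer that missed calls add to the undercount and, because the Discussion expects more attrition in the control arm, bias the comparison. The protocol does not support this. A missed call yields missing data, and the per-window odds are biased only if missingness is related to the outcome, which nothing in the text shows. The 26% in the sample size section and the attrition in the Discussion concern dropout, not intermittent missed calls. A woman who drops out has no later interview at which a reworded question could recover anything.

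**Conclusion.** The point holds as a defect of two printed questions. Their wording allows a truthful no to a new event from women whom the trial plainly enrolls, while the stated target is incidence in each 2-month window, and analysis cannot repair the result. The consequence is possible underestimation of pregnancy and STI incidence, with fewer events, in both arms.

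The size is unknown. Captures of 95%, 75% or 55% are illustrations from assumed shares, and no value should be reported as an estimate. No bias between arms is shown. The primary outcome does not use the phrase and is not affected. The under-reporting acknowledged in the Discussion is attributed to social desirability, which is a different mechanism.

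**What to change.** Before enrollment, delete the phrase from both items and ask about a new event, keeping the provider-told criterion and the 2-month window. Suggested wording: *In the past 2 months, has a healthcare provider told you that you have become pregnant?* and *In the past 2 months, has a healthcare provider told you that you have a new STI, such as chlamydia, gonorrhea or trichomonas infection?* Record the date of each event so that one pregnancy or STI episode is not counted at two calls. Align the outcome definition by replacing first occurrence with new occurrence. The per-window model can stay as written.

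Optionally, after a missed call, also ask about the time since the last completed interview, with dates, so that events can be assigned to the right window. This recovers intermittent misses only, not dropout, and lengthens recall for those women.

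The cost is rewording and retranslating two items, plus one date field for each.
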